### Secondary composite outcome

In a 1-year pilot study, 240 high risk Chinese T2D patients with CHD or multiple risk factors who have undergone CA using the JADE portal were randomized to usual care or structured

care group. In the latter group, supported by an endocrinologist and guided by a protocol, a diabetes nurse, assisted by a HCA, reviewed these patients every 3 to 4 months in addition to receiving usual care. At the end of 1 year, there were significant reductions in all risk factors in both groups, but more so in the team-based structured care group. The rate of attaining at least 2 of the 3 'ABC targets' increased by 2.5 fold from 15% to 37% in the structured care group while respective figures in the usual care were 20% to 28% with 1.4 fold increase, giving a 2 fold difference between the 2 groups. In the Hong Kong Diabetes Registry, type 2 diabetic patients who attained 2 of the 3 'ABC' targets had 50% risk reduction in incident CHD after a mean follow up period of 6 years (40).

| Change in risk factors at 1 year      | HbA1c (%) |    | Systolic BP (mmHg) |    | LDL-C (mmol/l) |    | body weight (%) |     |
|----------------------------------------------|-----------------------------|----|---------------------------|----|-----------------------|----|------------------------|-----|
| Effect size (reduction compared to baseline) | 0.5                         | 1  | 5                         | 10 | 0.5                   | 1  | 3                      | 5   |
| Structured care (%)                          | 77                          | 61 | 46                        | 35 | 32                    | 16 | 16                     | 8.7 |
| Usual care (%)                               | 60                          | 44 | 29                        | 18 | 26                    | 9  | 6                      | 2.6 |
| Between group Difference (%)                 | 17                          | 17 | 17                        | 17 | 6                     | 7  | 10                     | 6   |

In a multicentre randomized study involving Chinese type 2 diabetic patients with chronic kidney disease, 61% of patients receiving team-based structured care achieved 3 or more treatment goals (HbA1c<7%, LDL-C<2.6 mmol/l, BP<130/80 mmHg, triglyceride<2 mmol/l and persistence with ACE inhibitor or AII receptor blockers) compared to 28% in the usual care group, i.e. 2-fold increase. Patients who attained 3 or more treatment targets had 50% risk reduction of dialysis or ESRD at 2 year (29).

Based on these observations, we assume that the rate of attaining at least 2 'ABC' goals will increase by 2-fold compared to 50% in the usual care group and assuming 20% attrition rate, we estimate that 295-1814 patients will give the study sufficient power depending on the baseline rate of attaining 2ABC goals. In the first year analysis of the Asia Pacific JADE Program, 12-36% of patients attained at least 2 treatment goals with an average value of 30%.

|                                   | Total
(3687) | HK
(832) | India
(788) | Korea
(295) | Ph
(1186) | Sing
(256) | TW
(55)  | Thai
(275) |
|-----------------------------------|-----------------|-------------|----------------|----------------|--------------|---------------|-------------|---------------|
| HbA 1c <7%             | 35.3            | 61.8        | 13.8           | 40.7           | 31.3         | 35.2          | 25.5        | 29.8          |
| BP<130/80
mmHg                 | 32.3            | 45.6        | 26.0           | 38.3           | 27.2         | 12.9          | 34.6        | 42.9          |
| LDL-C<2.6
mmol/L               | 34.0            | 39.2        | 44.8           | 33.6           | 20.5         | 29.7          | 20.0        | 52.7          |
| No target
achieved     | 32.6     | 14.3 | 38.3    | 28.1    | 42.2  | 42.8   | 40.0 | 23.3   |
| Any 1 target
achieved          | 38.7            | 37.1        | 40.6           | 36.6           | 39.2         | 37.9          | 43.6        | 37.5          |
| Any 2 targets
achieved         | 23.4            | 36.3        | 19.2           | 29.8           | 16.2         | 15.2          | 12.7        | 29.8          |
| All 3 targets
achieved | 5.4      | 12.3 | 1.9     | 5.4     | 2.5   | 3.1    | 3.6  | 9.5    |

We also estimate the sample size needed to confirm the benefits of team-based care on controlling multiple risk factors. Apart from LDL-C goal, which can readily be achieved by initiating patients on statin therapy and thus requires a larger number to detect the small difference between the usual care and structured care groups, we estimate that 300-600 patients will be needed to confirm the superior effects of structured care. Given the expected heterogeneity in clinic settings, patient profiles and health care systems amongst different sites, a sample size of 600 patients will give each site sufficient power to confirm the superior effects of team-based structured care within their own clinic setting.

|                                         |      |      |      |
|-----------------------------------------|------|------|------|
| % of patients at 2 ABC goals in JADE-AP | 0.36 | 0.3  | 0.12 |
| SC (increased by 2-fold)                | 0.72 | 0.6  | 0.24 |
| UC (increased by 50%)                   | 0.54 | 0.45 | 0.18 |
| absolute difference                     | 0.18 | 0.15 | 0.06 |
| 80% at 0.05 alpha each group            | 123  | 186  | 756  |
| total sample size                       | 246  | 372  | 1512 |
| assuming 20% attrition rate             | 295  | 446  | 1814 |
| number needed to treat                  | 6    | 7    | 17   |

| Risk factors
units                          | A1c
% | A1c
% | SBP
mmHg | SBP
mmHg | LDL-C
mmol/l | LDL-C
mmol/l | BW   | BW    |
|------------------------------------------------|----------|----------|-------------|-------------|-----------------|-----------------|------|-------|
| reduction in risk factors compared to baseline | 0.5      | 1        | 5           | 10          | 0.5             | 1               | 0.03 | 0.05  |
| proportion of patients in SC                   | 0.77     | 0.61     | 0.46        | 0.35        | 0.32            | 0.16            | 0.16 | 0.087 |
| proportion of patients in UC                   | 0.6      | 0.44     | 0.29        | 0.18        | 0.26            | 0.09            | 0.06 | 0.026 |
| absolute difference                            | 0.17     | 0.17     | 0.17        | 0.17        | 0.06            | 0.07            | 0.1  | 0.061 |
| 80% at 0.05 alpha each group                   | 128      | 146      | 138         | 117         | 930             | 378             | 172  | 256   |
| total sample size                              | 256      | 292      | 276         | 234         | 1860            | 756             | 344  | 512   |
| assuming 20% attrition rate                    | 307      | 350      | 331         | 281         | 2232            | 907             | 413  | 614   |
| number needed to treat                         | 6        | 6        | 6           | 6           | 17              | 14              | 10   | 16    |

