**ABSTRACT**

**Rationale:** Change of practice environment and an interdisciplinary team is needed to implement evidence-based diabetes care which requires risk stratification, periodic assessments, education and treatment to targets.

**Hypothesis:** The use of a web-based disease management program (Joint Asia Diabetes Evaluation (JADE) Program) delivered by a doctor-nurse-HCA team reduces the incidence of all diabetes-associated clinical endpoint and improves control of risk factors compared to usual care (DIAbetes MONItoring Database (DIAMOND) group) in type 2 diabetes.

**Objective:** To compare structured care using the JADE portal versus usual care using the DIAMOND portal on incidence of all-diabetes related events, physical and psychological health.

**Study design:** A multicentre, randomized, integrated disease management program

**Setting and patients:** 600 patients from each site will be randomized to the JADE group (n=300) or the DIAMOND group (n=300) and followed up for at least 24 months.

**Intervention:** All patients will undergo comprehensive assessment (CA) guided by the templates in the respective portal at baseline, month 12 and 24. The JADE group will be further managed by a doctor-nurse-HCA team guided by the JADE portal with risk stratification program and recommendation to different care protocols with predefined follow up (FU) schedules, information sharing and decision supports.

**Outcome measures:** Primary composite outcomes include all diabetes-related clinical events; secondary composite outcomes include control of risk factors and tertiary composite outcomes include behavioral changes, psychological health, quality of life and cost-effective analysis.

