## **DATA ANALYSIS**

All data will be analyzed using the SPSS statistical software (Windows 13.0 version, Chicago, USA). A p value of 0.05 or less (2-tailed) will be considered significant. For the primary composite endpoint, an intention to treat analysis will be performed including all patients randomized to both groups who have at least returned for one visit or contacted by phone once post randomization to ascertain clinical status (alive, dead or hospitalized). Descriptive analysis will be used to report all clinical and laboratory parameters. Student's t-test, Chi-squared test and Analysis of Co-variance will be used for between-group and within-group comparisons for all baseline data and endpoints, as appropriate. Kaplan-Meier curve analysis will be used to compare the incidence of primary composite endpoint between the JADE and DIAMOND group adjusted for age, sex, ethnicity and disease duration. Interaction between group assignment and covariates including age, gender, duration of diabetes (< or ≥8 years), socioeconomic group, complications, risk factors, JADE risk categories, compliance and psychological health parameters will be examined. Logistic regression will be used to determine independent predictors for achieving primary composite endpoint using all relevant covariates including age, gender, duration of diabetes (< or ≥8 years), centre characteristics, socioeconomic group, risk levels, metabolic and risk factor control, compliance, self care, psychological health parameters and intervention groups.

A per protocol analysis will be performed in the JADE group with details of intervention, where we shall compare baseline clinical profile, care processes, number of visits and use of medications between patients who develop and those who do not develop clinical endpoints. A sensitivity analysis will also be performed using hazard rates of the JADE and DIAMOND group amongst those who have defaulted.

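### The per-site power claim for 600 patients fails where few patients meet two ABC targets at baseline, and the quoted 12-36% range counts exactly two targets, not at least two

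*Protocol*

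**What the plan says.** All places are in the Protocol.

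- **Abstract:** each site contributes 600 patients, 300 per group ("600 patients from each site will be randomized to the JADE group (n=300) or the DIAMOND group (n=300").
- **Secondary composite outcome, baseline rate:** in the first-year registry data, "12-36% of patients attained at least 2 treatment goals with an average value of 30"%. A country table follows, with rows for none, any one, any two and all three targets met.
- **Same section, sample size:** attainment is assumed to double under structured care and to rise by half under usual care. After 20% attrition, "we estimate that 295-1814 patients will give the study sufficient power depending on the baseline rate of attaining 2ABC goals". The table applies this at baselines of 0.36, 0.30 and 0.12. It gives 123, 186 and 756 per group, or 295, 446 and 1,814 in total with attrition.
- **Same section, per-site claim:** after an estimate of 300-600 patients for the single risk factors, with LDL-C excepted, the text concludes that "a sample size of 600 patients will give each site sufficient power to confirm the superior effects of team-based structured care" within its own clinic.
- **Data Analysis:** "A p value of 0.05 or less (2-tailed) will be considered significant".

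**The concern.** Two statements do not fit the plan's own figures.

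First, the per-site claim carries no condition, yet the ABC table shows that the required number depends heavily on baseline attainment and reaches three times 600 at the low end.

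Second, the range said to describe at least two targets coincides with the row for any two targets (12.7 in Taiwan to 36.3 in Hong Kong). That row excludes patients who met all three. The 30% average does fit at least two. One sentence and one table therefore mix two definitions.

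At stake is what sites are told. The Intellectual Property section lets investigators report their own clinic's data after the multicentre results, with steering committee approval. A site assured of adequate power could read a null local result as evidence of no benefit when its chance of detecting the planned difference was little better than even.

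**Working it through.** **Step 1. Reproduce the plan's figures.** Inputs: two-sided 0.05, 80% power, 1:1 allocation, structured care (SC) = 2 × baseline, usual care (UC) = 1.5 × baseline. With d = p1 − p2 and p̄ the mean of the two rates:

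n0 = [1.96·√(2p̄(1−p̄)) + 0.8416·√(p1(1−p1) + p2(1−p2))]² / d²

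n = (n0/4)·[1 + √(1 + 4/(n0·d))]² (continuity-corrected)

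| Baseline | SC v UC | n0 | n per group | Total | × 1.2 |
|---|---|---|---|---|---|
| 0.36 | 0.72 v 0.54 | 111.8 | 123 | 246 | 295 |
| 0.30 | 0.60 v 0.45 | 172.8 | 186 | 372 | 446 |
| 0.12 | 0.24 v 0.18 | 722.2 | 756 | 1,512 | 1,814 |

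All three columns match exactly. The plan inflates by × 1.2. Dividing by 0.8 would give 308, 465 and 1,890, about 4% more; this is a side point.

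**Step 2. Power of 600 patients in the plan's 12% column.** Power = Φ{[d√n − 1.96·√(2p̄(1−p̄))] / √(p1(1−p1) + p2(1−p2))}, without continuity correction and so slightly optimistic.

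- n = 300 per arm: (0.06 × 17.321 − 1.96 × 0.5760)/0.5745 = −0.156, power 44%.
- n = 240 per arm (20% loss): (0.06 × 15.492 − 1.96 × 0.5760)/0.5745 = −0.347, power 36%.

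**Step 3. What the registry rows mean.** If the four rows are exclusive, they sum to 100, and (any 1) + 2 × (any 2) + 3 × (all 3) equals the sum of the three single-target rates.

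- The four rows sum to 99.0-100.1 in every column.
- Hong Kong: 37.1 + 2 × 36.3 + 3 × 12.3 = 146.6, and 61.8 + 45.6 + 39.2 = 146.6.
- Total: 38.7 + 2 × 23.4 + 3 × 5.4 = 101.7, and 35.3 + 32.3 + 34.0 = 101.6.
- The other six columns agree within 0.3 points.

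The any-two row therefore means exactly two. At least two = any 2 + all 3: Taiwan 16.3, Singapore 18.3, Philippines 18.7, India 21.1, Korea 35.2, Thailand 39.3, Hong Kong 48.6, total 28.8.

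**Step 4. Repeat with at-least-two rates and the plan's 2.0-fold and 1.5-fold increases.**

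| Setting | Baseline | SC v UC | n per group | Total × 1.2 | Power, 300/arm | Power, 240/arm |
|---|---|---|---|---|---|---|
| Taiwan | 0.163 | 0.326 v 0.2445 | 505 | 1,212 | 60% | 51% |
| Singapore | 0.183 | 0.366 v 0.2745 | 429 | 1,030 | 67% | 57% |
| Philippines | 0.187 | 0.374 v 0.2805 | 416 | 998 | 69% | 59% |
| India | 0.211 | 0.422 v 0.3165 | 346 | 830 | 76% | 67% |
| All | 0.288 | 0.576 v 0.432 | 202 | 485 | 94% | 89% |
| Korea | 0.352 | 0.704 v 0.528 | 130 | 312 | 99% | 98% |

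Thailand exceeds 99% in both power columns. For Hong Kong, doubling 0.486 gives 0.972, so the doubling rule does not give a credible planning rate there.

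**Step 5. Baseline at which 600 patients reach 80% power.** About 22% with no loss (300 per arm) and 25.4% with 240 per arm. By the continuity-corrected formula it is 25.7% with the plan's × 1.2 and 26.3% with ÷ 0.8. After 20% attrition, the threshold is about 25-26%.

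**The case against.** Several points on the other side stand and limit the finding.

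- **The ABC table is not labelled per site.** The text attaches 295-1,814 to the study as a whole. A reader might infer that the plan states a per-site need of 1,814 and then contradicts it. It does not. The error is an unconditional per-site sentence beside a table showing that the need varies with baseline.
- **The 600 sentence follows the single-risk-factor estimate.** Outside LDL-C, which is openly excepted, those rows need 281-614, so 600 roughly fits them. But the sentence is general and makes no exception for sites with low ABC attainment.
- **The 1,814 comes from the misread rate.** Correcting the rates improves the low end: the worst case falls to about 1,212, and power with no loss rises from 44% to 60%.
- **The secondary endpoint is wider.** Outcome Measures defines it as two or more ABC targets and/or two of four risk-factor changes. A reader might infer that the secondary endpoint itself is underpowered at these sites. The documents do not show that, because no rate or power is given for the full composite. For the same reason, the composite cannot support the per-site claim.
- **600 does not drive the size of the whole trial.** The primary endpoint is sized separately (6,626-13,762 for the high- and medium-risk scenarios), and the risk-equation validation gives 596 per centre.
- **The multicentre conclusion is not threatened.** Data Analysis specifies no site-level test. The number of sites is not stated; if five sites gave 3,000 patients, then even at 24% v 18% with 1,200 per arm after 20% loss, pooled power would be about 95%.
- **Country averages only approximate site rates.** Taiwan has 55 patients: about 9 met at least two targets, with an exact 95% interval of roughly 8-29%, which spans the threshold.

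**Conclusion.** The concern holds as an incorrect label and an over-broad power statement. The label follows from the table's own arithmetic and needs no assumption: 12-36% is the exactly-two range, and only the 30% average is consistent with at least two.

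The per-site claim is wrong as written at the plan's own 12% column, and stays wrong after correction for sites with baselines like those of four of the seven settings. That second result assumes the plan's 2.0-fold and 1.5-fold increases, two-sided 0.05, 1:1 allocation, 20% attrition, and country rates standing in for site rates. It concerns the ABC limb only.

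Severity: should-fix. It affects what sites are told about their own data, not the primary endpoint or the pooled secondary comparison.

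**What to change.** 1. Relabel 12-36% as exactly two targets, or replace it with the at-least-two range of 16.3-48.6% (28.8% overall).
2. Recompute the ABC table with at-least-two rates: 0.163 at the low end (505 per group, 1,212 with the plan's × 1.2) and 0.288 overall (202 per group, about 485). At the high end, state an explicit attainable structured-care rate in place of doubling; the 0.486 column cannot be usefully computed without one.
3. Replace the per-site claim with a conditional one: after 20% attrition, 600 patients give at least 80% power for attaining two or more ABC targets only where baseline attainment is about 25-26% or more. Below that, site-level results are reported as estimates with confidence intervals.
4. Say that these figures cover the ABC limb and not the full composite.

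The cost is a corrected table and a few sentences. Compared with the present claim, the stated power becomes less favourable for low-attainment sites. Enrolment does not change.

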#### Validation of risk equations derived from the Hong Kong Diabetes Registry

Assuming a 2% annual incidence of all diabetes-related event rates including death, stroke, heart disease, lower extremity amputation, visual impairment, renal failure and cancer, i.e. 4% in 2 years, a sample size of 596 will confirm this estimate with an error of 1% for each

participating centre. In our previous analysis, we have shown that the UKPDS risk engine under-estimated the stroke rate and, over-estimated the CHD rates in Chinese type 2 diabetic patients. Furthermore, compared to our risk equations, UKPDS does not utilize important risk parameters such as eGFR, ACR and blood hemoglobin which are powerful predictors of clinical endpoints in Asian populations (41) (42).

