1 Cardiovascular-renal complications: cardiovascular diseases (stroke, coronary heart disease and/or peripheral vascular disease with or without interventions or medications), heart failure and end-stage renal diseases [on renal replacement therapy or estimated glomerular filtration rate (eGFR) < 15 ml/min 1.73/m^2].

2 Risk score: high sensitivity (ST) and specificity (SP) cut-off points, derived from each of the four risk equations of the Hong Kong Diabetes Registry, were used to estimate probability of risk of clinical outcomes.

3 Stratification parameters: Current or ex-smoker; body mass index ≥ 27.5 kg/m^2 or waist circumference ≥ 80 cm in women or ≥ 90 cm in men; blood pressure > 130/80 mmHg or treatment with antihypertensive drugs; low-density lipoprotein-cholesterol (LDL-C) > 2.5 mmol/l; triglyceride (TG) ≥ 2.3 mmol/l and/or high-density lipoprotein-cholesterol (HDL-C) < 1.0 mmol/l; treatment with lipid-regulating drugs if LDL-C ≤ 2.5 mmol/l and TG < 2.3 mmol/l and HDL-C ≥ 1.0 mmol/l; random spot urinary albumin-creatinine ratio > 3.5 mg/mmol in women or > 2.5 mg/mmol in men; foot at risk defined by two of three of the following: sensory neuropathy, skin changes (e.g. fungal infection, dry skin) or deformities (e.g. claw feet or hallux deformities); retinopathy; HbA1c ≥ 8%.

4 eGFR in ml/min 1.73/m^2.

Risk levels:

1 Level 4: Presence of any cardiovascular or renal complication.

2 Level 3: No cardiovascular or renal complication; and either having three or more stratification parameters, or risk scores above the high specificity cut-off in any one of the risk equations, or eGFR < 60 ml/min 1.73/m^2.

3 Level 2: No cardiovascular or renal complication; none of the conditions (risk score, stratification parameters, eGFR) defined in the 'High risk' category but not belonging to the 'Low risk' category.

4 Level 1: No cardiovascular or renal complication; and having other condition fulfilling the 'Low risk' (one or less stratification parameter, and risk scores below the high sensitivity cut-off in all of the risk equations, and eGFR ≥ 90 ml/min 1.73/m^2).

- 2) After the patient has undergone CA, the nurse will arrange 2-4 hours of diabetes education in groups or individually and explain the various features of the JADE report.

[figure not shown]

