|          |                     | 19%            | cataract        |
|          |                     | 37%            | microvascular   |
|          |                     | 43%            | PVD             |

| Steno 13 year FU       | SC=80 | UC=80 | HR   |
|------------------------|-------|-------|------|
| death                  | 24    | 40    | 0.50 |
| CVD-death              | 9     | 18    | 0.23 |
| MI                     | 8     | 21    | 0.26 |
| stroke                 | 6     | 18    | 0.23 |
| PCI                    | 8     | 13    | 0.16 |
| revascularization      | 6     | 10    | 0.13 |
| amputation             | 6     | 14    | 0.18 |
| all CVD events         | 25    | 48    | 0.60 |
| cancer-death           | 2     | 5     | 0.06 |
| DM nephropathy         | 20    | 37    | 0.46 |
| ESRD                   | 1     | 6     | 0.08 |
| Blindness              | 2     | 7     | 0.09 |
| Progression of DMR     | 41    | 54    | 0.68 |
| Laser or macular edema | 14    | 27    | 0.34 |

| 2-year SURE Study | ≥3 target | <3 targets | HR   |
|-------------------|-----------|------------|------|
| ESRD/death/dSeCr  | 14        | 34         | 0.30 |
| dialysis          | 6         | 12         | 0.11 |
| dSeCr             | 10        | 21         | 0.18 |
| death             | 4         | 15         | 0.13 |
| MI/angina/PCI     | 4         | 7          | 0.06 |
| heart failure     | 12        | 16         | 0.14 |

| 7-year AJMC paper | SC | UC | HR   |
|-------------------|----|----|------|
| death             | 8  | 20 | 0.25 |
| death/CVS/renal   | 20 | 30 | 0.38 |

These Kaplan-Miere plots show the estimated events from these 3 studies in a 2-year period.

Chinese T2D patients with CKD (eGFR 30 ml/min/1.73m^2)  
Chan JC et al Diabetes Care 2009

[figure not shown]

Chinese T2D patients with HT (no CVD/CKD)  
So WY et al Am J Managed Care 2003

[figure not shown][figure not shown]

Caucasian T2D patients with microalbuminuria (no CVD/CKD)  
Gaede P et al NEJM 2008

[figure not shown]

Using validated risk equations and risk parameters, the JADE Program stratified patients into very high risk, high risk, medium risk and low risk groups with respective estimated annual event rate of 7%, 3%, 1.5% and 1%.

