#### Risk levels (5-year event rate)

4: Cardio-renal complications

3: CKD or at least 3 risk factors or high risk score

2: no CKD and 2 risk factors or medium risk score

1: no CKD and 1 or no risk factor and low risk score

Chan JC et al Diabetic Med 2009

In our first year analysis of the JADE Asia Pacific Program, the majority of enrolled patients from 7 countries belonged to very high to high risk category.

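### The section on validating the risk equations gives only a per-centre precision calculation for one assumed composite incidence, which cannot show whether any equation predicts well

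*Protocol*

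**What the plan says.** The relevant text is the last subsection of Sample Size Calculation in the Protocol, headed "Validation of risk equations derived from the Hong Kong Diabetes Registry". It begins "Assuming a 2% annual incidence of all diabetes-related event rates including death, stroke, heart disease, lower extremity amputation, visual impairment, renal failure and cancer" and continues "i.e. 4% in 2 years, a sample size of 596 will confirm this estimate with an error of 1% for each" participating centre. The rest of the subsection explains why the Hong Kong equations are preferred to another risk engine, which, in the sponsor's earlier analysis, "under-estimated the stroke rate and, over-estimated the CHD rates in Chinese type 2 diabetic patients".

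Three other places bear on it.

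- **Intervention – JADE Group:** the risk-score cut-offs are "derived from each of the four risk equations of the Hong Kong Diabetes Registry", so four separate prediction equations are in use.
- **Primary composite outcome:** the four JADE risk levels have estimated annual event rates of 7% (very high), 3% (high), 1.5% (medium) and 1% (low). The text below Risk levels adds that most patients in the first-year analysis were at high or very high risk.
- **Data Analysis:** risk categories appear among the interaction covariates, and risk levels among the covariates of a logistic model for the primary endpoint. No comparison of observed with predicted risk is described.

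**The concern.** Validating a risk equation means comparing what it predicts for each patient with what then happens. Calibration asks whether the predicted number of events occurs. Discrimination asks whether patients with higher predicted risk have more events. The quantity fixed here is neither. It is the precision with which one centre can estimate a single event rate around a value chosen in advance.

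This is more than detail left to a later document. Under a validation heading, the Protocol states a target quantity, a sample size and a unit (the centre), and the quantity is the wrong one for that purpose. If the validation is later reported on this basis, a rate near 4% could be offered as support for equations that were never tested.

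**Working it through.** **1. The plan's own figure.** Inputs from the validation subsection are p = 0.04, error e = 0.01 and n = 596 per centre. The confidence level is not given there; 95% is assumed from Data Analysis ("A p value of 0.05 or less (2-tailed) will be considered significant").

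n = z²p(1−p)/e² = 1.96² × 0.04 × 0.96 / 0.01² = 1475.1, so 1476.

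The stated 596 is not reproduced. At 90% confidence n is 1039 and at 80% it is 631. With p = 0.02 and 95% it is 753. The figure 596 appears only with a finite-population correction for N = 1000, which the Protocol does not mention: 1475.1 / (1 + 1474.1/1000) = 596.2. With 596 patients the 95% half-width at 4% is 1.96 × √(0.04 × 0.96/596) = 1.57 points. This is a separate error. The present point would stand if the arithmetic were right, but the attempt confirms that the calculation is a one-proportion precision formula with no term for predicted risk.

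**2. Is the 2% a prediction from the programme's risk estimates?** Assume that the level-specific rates count broadly the same events as the seven-type composite; the readable text does not say. If more than half of patients are at level 3 or 4, the lowest possible mean has the majority at level 3 and everyone else at level 1:

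0.5 × 3% + 0.5 × 1% = 2.0% a year.

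Any larger majority, or any patient at level 4 or 2, raises it. The mix is not given in the readable text, so two assumed mixes over levels 4, 3, 2 and 1 show the range:

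- 30/40/20/10%: 0.3 × 7 + 0.4 × 3 + 0.2 × 1.5 + 0.1 × 1 = 3.7% a year, or 7.4% in 2 years (doubling, as the Protocol does).
- 40/40/10/10%: 2.8 + 1.2 + 0.15 + 0.1 = 4.25% a year, or 8.5% in 2 years.

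In a 600-patient centre, 4% is 24 events. The programme's rates would predict 600 × 0.074 = 44.4 or 600 × 0.085 = 51. Observing 24 matches the Protocol's estimate exactly, yet observed/expected is 24/44.4 = 0.54 or 24/51 = 0.47. The check can be met while the programme's own estimates are far out, with no offsetting errors needed.

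**3. Can a composite reveal errors in opposite directions?** No. Take assumed two-year rates, chosen only to show the arithmetic:

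| | Observed | Predicted |
|---|---|---|
| Stroke | 1.5% | 0.75% |
| CHD | 1.0% | 1.75% |
| Other | 1.5% | 1.5% |
| Total | 4.0% | 4.0% |

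Stroke is under-predicted by half and CHD over-predicted by 75%, but the totals agree. This is the pattern that the same subsection reports for the other risk engine.

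**4. What could one centre, or all centres, support?** An approximate 95% interval for observed/expected when the two are equal is exp(±1.96/√O). Even if all 24 events in a centre belonged to one equation, 1.96/√24 = 0.400, giving 0.67 to 1.49. That is a best case for a single centre.

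Pooled, use the Protocol's table at hazard ratio 0.8 before attrition. The high-risk scenario gives 3313 × (0.10 + 0.08) = 596 events (equal to the other 596 only by coincidence). The moderate-risk scenario gives 5734 × (0.06 + 0.048) = 619. If all belonged to one equation the interval would be about 0.92 to 1.08. Each equation would have only a share of these, and the readable text does not give the split. Pooling is nevertheless clearly the more useful unit.

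**The case against.** The strongest reply is that this is a sample-size remark, not a decision rule. What the 596 patients are said to confirm is the 2% or 4% incidence, not the equations. A reader might infer that a centre with a rate near 4% would declare the equations confirmed, and that a centre far from 4% would reject them. The Protocol says neither, so that reading is not supported.

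Secondly, validation is not among the hypotheses, objectives or endpoints, and calibration and discrimination methods are commonly left to an analysis plan. This stands as far as missing method detail goes. It does not cover a stated quantity, sample size and unit that do not serve the stated purpose; an analysis plan that added calibration would leave this justification wrong.

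Thirdly, the remark about the other risk engine treats stroke and CHD separately, which suggests that the sponsor already judges risk engines outcome by outcome. That is fair as to intention, but the calculation given does not follow it.

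Finally, a reader might infer that a false validation would feed into patient triage. The documents do not support this. The Protocol already treats the equations as validated and in use, triage also depends on complications, stratification parameters and eGFR, and no action in the trial depends on the outcome of this subsection.

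**Conclusion.** The mismatch is real: the heading promises validation of the risk equations, and the text supplies precision for one assumed composite rate per centre. The calculation uses no predicted risk, merges seven event types although there are four equations, and rests on a 2% annual rate below what the programme's level-specific rates imply for a mainly high-risk population. An observed rate near 4% would not show that any equation is calibrated or ranks patients correctly.

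The point is ancillary: worth correcting, but minor. The randomised comparison of JADE with DIAMOND is unaffected. The conclusion about the target quantity needs no numerical assumption. The comparison with the level-specific rates assumes that trial centres resemble the first-year population and that both sets of rates count similar events. The mixes in step 2 and the component rates in step 3 are illustrations, not estimates.

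**What to change.** Retitle the 596 calculation as precision of the two-year composite incidence at a centre, and stop presenting it as the basis for validation. Its arithmetic should be corrected at the same time.

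If validation is intended, state it for each equation:

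- include patients free of that equation's outcome at baseline;
- calculate each patient's predicted risk, rescaled to the follow-up observed (about 2 years; the programme presents its risk levels on a 5-year scale);
- report the observed/expected ratio, overall and by predicted-risk group, and the c-statistic, each with a 95% interval;
- pool over centres and show the variation between them.

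Give the expected pooled precision per equation, using event rates that match the scenario behind the assumed total sample size and stating how many events each equation is expected to have. An even split over event types should not be used, because nothing in the documents supports it.

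The cost is a change of wording and some extra analysis. Comprehensive assessment already collects eGFR, albumin-creatinine ratio, a complete blood count and clinical events. What is lost is the per-centre precision statement as support for validation.
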